## Abstract

**Background:**

Reduced physical mobility is common in older adults and is associated with adverse outcomes, including functional decline, depression, social isolation, and poor nutritional status. Group-based programs focusing on physical activity and nutrition to support healthier lifestyles have demonstrated benefits, particularly when paired with social engagement activities. This paper presents the protocol for a randomized controlled trial (RCT) to test a lifestyle intervention called **EMBOLDEN**: a multifaceted intervention aimed at **E**nhancing physical and community **M**o**B**ility in **OLDE**r adults with health inequities using commu**N**ity co-design. EMBOLDEN is a co-designed 3-month intervention to improve quality of life by incorporating physical activity, healthy eating, social participation, and system navigation. Participants receiving the EMBOLDEN intervention plus usual care are expected to show improvement in physical activity and other health outcomes compared to receiving usual care alone.

**Methods:**

This is a 2-arm Type II hybrid effectiveness-implementation pragmatic RCT. Eligibility criteria include older adults (55+ years), community-dwelling in urban neighborhoods facing health inequities, able to speak or understand English or Mandarin (or access to family/friend interpreters), and able to walk 10 m unassisted by another person (assistive devices permitted). Participants will be randomized to the intervention or control arm (1:1 ratio). The intervention arm is usual care plus: (1) 12 weekly group-based sessions to increase knowledge/skills and behavior activation related to physical activity, healthy eating, fostering social connections and community resources; and (2) up to three tailored individual system navigation sessions. The control arm is usual care, in which participants identify and access services without research support. The primary outcome is time spent doing moderate-to-vigorous physical activity. Secondary outcomes will also be explored, including quality of life, life space mobility, depressive symptoms, nutritional risk, and loneliness. Data will be collected at baseline, 3 months (post-intervention) and 6 months. Mixed effects models will be used to analyze outcomes, intention-to-treat analysis will be employed, and multiple imputation will address missing data. Descriptive and qualitative data from participants, interventionists, and research documentation will be used to examine adaptations and implementation barriers/facilitators.

**Discussion:**

A community-based, co-designed lifestyle intervention may improve physical activity and other health outcomes in older adults living in neighborhoods with health inequities.

**Clinical trial registration:**

ClinicalTrials.gov, NCT05008159.

## Introduction

1

### Background and rationale

1.1

Mobility is necessary for maintaining independence and quality of life as we age. Mobility is defined as the ability to “move oneself within community environments that expand from one’s home to the neighborhood and to regions beyond” and is a holistic concept defined by five domains—physical, cognitive, psychosocial, financial, and environmental (1). This definition of mobility has been measured by various life-space mobility tools that comprehensively assess everyday movement, with studies showing that healthcare costs and utilization steadily increase across declining life-space scores (2). Reduced physical mobility is common with aging and a recognized precursor to frailty (3), a multidimensional syndrome of reserve loss (e.g., energy, physical ability, cognition) that leads to functional decline (4). Frailty also has bidirectional relationships with depression, loneliness, social isolation (5), and poor nutritional status, which may increase morbidity and mortality risk in older adult (6). Social frailty is a progressive state of being vulnerable to the loss or deprivation of resources necessary to fulfill one’s basic social needs throughout life; it is indicated by four factors: degree of neighborhood interaction, living alone, social participation, and economic status (7). Social frailty is receiving increased attention because these factors are potentially modifiable and because of its association with a higher incidence of adverse health outcomes including disability, reduced neuropsychological function, and mortality (7, 8).

Multi-faceted group-based interventions aimed at improving physical activity and nutritional behavior in older adults have demonstrated well-established health benefits (9–12); however, optimal design features of such interventions have been poorly defined. The inclusion of social support/engagement and other behavior change strategies in group-based nutrition interventions have been shown to further enhance their effectiveness (13). Community programs encouraging healthy, active lifestyles and social engagement may be highly effective in improving physical mobility, nutritional status, and social participation, older adults often face barriers to accessing these programs (e.g., social isolation, social anxiety, physical barriers, cost and transportation, lack of awareness of existing services) (14). These concerns are particularly notable for those living in communities with high health inequities (15–17).

Challenges arise when attempting to mobilize evidence or replicate—in the real world—the promising effects of home- or community-based mobility-enhancing interventions tested in controlled settings. For example, The LIFE study’s interventions (11) involved walking and lower extremity strengthening exercises in older adults aged 70–89 years and were mildly successful in reducing disability risk. Yet, their numerous exclusion criteria related to the presence of conditions common to older people (e.g., cancer, mental health, heart disease, diabetes, hypertension, arthritis) suggest that more modest results will likely be achieved if translated to the general population. The SPRINTT trial employs a multi-component intervention to prevent mobility disability but uses a controlled lab setting for the exercise component, has had limited testing to date in real-world settings (18, 19), and has not been fully assessed for its implementation and sustainability (20).

Ideally, interventions to enhance physical activity, social participation, and healthy eating should be designed to allow for tailoring to an individual’s lifestyle and personal preferences to capture a more realistic and pragmatic approach, avoid a ‘one-size-fits-all’ model, and facilitate implementation and sustainability. Engaging target populations and research partners to co-design such interventions may ensure better alignment between research and existing community programs, leverageable assets, and the contextualized experiences of older adults (21). Input from knowledge users (e.g., older adults, health and social service providers in the community, organizational decision-makers) can support mobilizing knowledge into practice to maximize impact.

Little research has explored effective and appropriately targeted interventions for physical and community mobility in older adults in a real-world context. This study aims to fill this research gap through a novel program co-designed with older adults in alignment with their needs. The research design will be outlined in the following sections and presented following the SPIRIT guidelines for clinical trial protocols (22).

### Purpose and objectives

1.2

This protocol is for a randomized controlled trial (RCT) to test a novel intervention called **EMBOLDEN**: a multifaceted intervention aimed at **E**nhancing physical and community **M**o**B**ility in **OLDE**r adults with health inequities using commu**N**ity co-design. EMBOLDEN is a 3-month, co-designed, multifaceted, community-based primary prevention intervention incorporating physical activity, healthy eating, social participation, and system navigation. The primary objectives are to compare the effects between the intervention and control groups (usual care) on the primary outcome of physical mobility and to determine how the intervention was implemented and adapted across diverse urban neighborhoods. The secondary objectives are to compare the intervention and control groups on several secondary outcomes (e.g., life-space mobility, health-related quality of life, resilience, sense of community, nutrition status) and assess various implementation outcomes (e.g., adoption rate per protocol, intervention fidelity, feasibility and acceptability of the intervention to older adults and providers).

### Trial design

1.3

The trial design is a 2-arm parallel group Type II hybrid effectiveness-implementation pragmatic RCT. The allocation ratio is 1:1 for the intervention and control arms. The hybrid design places equal emphasis on simultaneously assessing implementation and effectiveness (23). Including key implementation-related outcomes (e.g., uptake, contextual implementation determinants, and adaptations) is consistent with recommendations for developing and evaluating complex interventions; early consideration of implementation increases the potential to extract more effective implementation strategies, rapid translational gains, and contextually relevant information for decision-makers (24). The trial is likely to produce results similar to those expected in practice as a pragmatic design was chosen to more closely replicate real-world conditions. Design features, such as eligibility criteria, recruitment, and flexibility of delivery and adherence, were selected to best align with practice (25). The following pragmatic features were included in the EMBOLDEN trial design:

i) recruiting a sample with broad inclusion criteria reflective of the general population of community-dwelling older adults;ii) conducting the study in existing community settings (e.g., community centers, recreation facilities);iii) leveraging existing resources, staff, and service delivery organizations in the intervention arm that are currently available in the real world setting;iv) supporting flexible delivery of the intervention (e.g., tailoring group-based strategies to participant group needs/interests/abilities and person-centerd tailoring of individual component), as would be done through other community programs in usual care;v) allowing flexibility in adhering to the intervention in ways that are consistent with usual care;vi) selecting primary and secondary outcomes that are participant-relevant (e.g., based on knowledge user input); andvii) using intention to treat analyses based on all available data.

### Research questions

1.4

The study is designed to answer several primary and secondary research questions. The primary research questions to be addressed are:

1 Effectiveness: Does the 3-month EMBOLDEN intervention plus usual care increase moderate to vigorous physical activity (MVPA) compared to usual care alone in community-dwelling older adults residing in areas of high health inequity?2 Implementation: How is the EMBOLDEN intervention implemented and adapted across diverse urban neighborhoods?

The secondary research questions are:

1 Effectiveness:

i What is the effect at 3 months and 6 months of the EMBOLDEN intervention plus usual care compared to usual care on other outcomes (i.e., other smartwatch-derived measures of physical activity such as steps and distance traveled, self-reported physical activity, life-space mobility, nutritional risk, food security, health services utilization, health-related quality of life, resilience, loneliness, sense of community belonging, and collective efficacy) in community-dwelling older adults residing in areas of high health inequity?ii If a significant treatment effect is observed for the primary outcome (MVPA), which subgroups of older adults benefit the most from the intervention?

2 Implementation:

i What is the adoption rate of the EMBOLDEN intervention (i.e., the proportion of participants enrolled in the study who attend at least one group session and receive at least one system navigation support session)?ii What intervention dose is received by participants (i.e., number of group sessions and individual support sessions attended)?iii Regarding recruitment:

a What is the recruitment rate for the trial, and how does the sample compare to the target population?b What strategies contribute to the successful reach of older adults living in areas with health inequities?

iv How do local community organizations involved in delivering EMBOLDEN view the adoptability of the program within their organization?v To what extent is the EMBOLDEN intervention implemented with fidelity, and what are the key implementation barriers and facilitators at individual, organizational, and community levels that impact fidelity?vi How feasible and acceptable is the EMBOLDEN intervention to participants and interventionists?vii How do participants and interventionists describe their experiences with EMBOLDEN, including satisfaction and perceived impacts of the intervention?viii What factors are considered critical to the successful sustainment and scaling of the intervention?

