##### EMBOLDEN

2.1.3.1

**Theoretical underpinning**: The intervention and its core components are shaped by social cognitive theory targeting behavioral change through tailored and group-based approaches (30). An adapted experience-based co-design process with community-dwelling older adults and health and social service providers who were members of the SGC was used to refine and operationalize core intervention components (see below) (21). Qualitative research suggests co-design processes contribute to positive impacts at the participant, provider, and organizational levels (31). Our co-design process supported identifying key design features aligned with older adults’ priorities, delivery processes to match their preferences and ‘emotional touchpoints’ (i.e., maximizing positive experiences and addressing negative emotions that may be barriers to engagement). The co-design process used to engage the SGC has been evaluated. This included responses from a questionnaire, focus groups, and document analysis of meeting notes from 16 SGC meetings. Participants noted the strength of diversity within the SGC and engagement processes were perceived as inclusive and well-facilitated. The important impacts of the SGC in the preparation, execution and translational stages of EMBOLDEN were described by all participants, as well as the personal benefits of being involved as a member of the SGC (32).

**Core components:** The EMBOLDEN intervention will consist of usual care (see below) plus the following two core components: 12 weekly interactive group sessions and individually tailored 1:1 system navigation support. Both components will be delivered by the intervention team consisting of trained EMBOLDEN program facilitators who work in existing roles in community organizations and institutions (e.g., primary care interdisciplinary team members, municipal public health units, and municipal recreation departments).

As part of the program, we have engaged real-world providers who work for organizations that deliver similar types of programs, typically as one or occasionally two component(s) of the EMBOLDEN program. We offer the program in existing publicly funded facilities that operate within or nearby the neighborhoods (when a facility did not exist within the boundaries). We negotiated these partnerships and ensured alignment with their organizational mandates as part of the pragmatic trial to lay the foundation for sustainability.

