	-Utilization of community programs/resources	t_1_, t_2_, t_3_ t_3_ up to 3 (start, mid- and end of group-based program)	End of study survey (all intervention participants) Interviews (subset of intervention participants) Genie® (intervention participants)
	-Social network analysis variables (e.g., size of the network, diversity of the network, number of strong/weak ties, number of hobby or community groups).	t_1_, t_2_, t_3_	Genie® (intervention participants)
Adoption (Organization level)	-# and % of community partners approached that join Strategic Guiding Council (SGC)	t_1_, t_2_, t_3_	SGC Recruitment Logs
	-Reasons for non-participation in SGC	t_1_, t_2_, t_3_	SGC Recruitment Logs
	-# and % of community partners retained in SGC	t_2_, t_3_	SGC Recruitment Logs
	-Reasons for discontinuation on SGC	t_2_, t_3_	SGC Recruitment Logs
	# and % of community partners approached and joined Community Advisory Board (CAB)	t_1_, t_2_, t_3_	CAB Recruitment Logs
	-Reasons for non-participation on CAB	t_1_, t_2_, t_3_	CAB Recruitment Logs
	-# and % of community partners retained in CAB	t_2_, t_3_	CAB Recruitment Logs
	-Reasons for discontinuation on CAB	t_2_, t_3_	CAB Recruitment Logs
	-# Community partners who agree to participate in intervention delivery among those approached	t_1_, t_2_, t_3_	CAB Recruitment Logs
	-# Trained interventionists within each neighborhood	t_1_, t_2_, t_3_	CAB Recruitment Logs
I (Implementation, organization level)	-Fidelity of delivery (% of core content delivered in group-based intervention sessions, content delivered during system navigation sessions)	t_2_	Group Session Checklist
	-Adaptations at local sites	t_1_, t_2_	Research Team Meetings with Interventionists (notes)
	-Barriers and facilitators to implementation	t_2_, t_3_	Research Team Meetings (notes) and Focus Groups with Interventionists (transcripts of audio-recordings) Interviews (intervention participants) CAB, SGC Meeting Notes
	-Cost of delivery (per participant, group, site)	t_1_, t_2_	Study Budget
M (Maintenance. Organization level)	-# Community partners intending to offer the program 3 months after study discontinuation^b^ ^−^Reasons for program cessation	t_3_	Key informant interviews

a t_1_ = baseline, beginning of study; t_2_ = 3 months, post-intervention; t_3_ = 6 months, end of study.

b The timeframe for assessing maintenance in RE-AIM is 6 months post-intervention. We adjusted the timeframe to 3 months to align with our final data collection timepoint (t_3_).

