
All participants enrolled in the study, regardless of group allocation, will receive one $25 gift card for each quantitative data collection interview completed, for a maximum of three gift cards. This information is stated in all recruitment materials. Honoraria are provided to enhance recruitment by providing incentives to participate and mitigate attrition, particularly in the control group.

A cohort approach to recruitment and entry into the program will be adopted to foster socialization and relationship building (i.e., we aim to recruit all participants for a neighborhood to start within the first few weeks to allow intervention group participants opportunities to build relationships and socialize over the course of the program). One cohort will be rolled out per neighborhood with a maximum of 50 participants (25 intervention, 25 control) to be enrolled in each Hamilton (*n* = 8) and Toronto neighborhood (*n* = 2). Individual baseline data will be collected as individuals are enrolled in the study. The Research Coordinator will create monthly summary reports to enable the research team to determine whether recruitment targets are being met and whether additional targeted methods are needed to reach underserved groups. The final evaluation report will include the absolute number and percentage of individuals who responded to recruitment requests, enrolled, and retained in the program, as well as reasons for exclusion and dropout and comparison to the neighborhood characteristics collected through census data (see Table 1—RE-AIM outcomes and Table 2—Participant Timeline).

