#### Allocation

2.2.1

The unit of randomization is the individual participant. The aim is to recruit 50 individuals in each neighborhood; these individuals will be randomized to receive the EMBOLDEN intervention versus usual care with a 1:1 ratio (25 individuals per trial arm at each site). The allocation process will use a randomized block design with three permuted block sizes (2, 4, 6). A biostatistician will generate the randomization sequence at each site using the *blockrand* package in R version 4.4.1.

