#### Allocation concealment and implementation

2.2.2

The random number sequences for each site will be input into a central web-based service (REDCap®) that allocates participants to the two study arms in accordance with the sequence. Once the randomization sequences for each site are set up in REDCap, the system will be moved to production mode, which locks the randomization model, thereby ensuring that the sequence is not modified once the project begins. A Research Assistant will screen participants for eligibility and obtain consent from those who accept an invitation to participate (see Supplementary material for consent form). Once informed consent is obtained, the participant will be enrolled, baseline data will be collected, and the Research Coordinator will then obtain the participant’s group allocation from REDCap.

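### The participant adoption rate is defined over everyone enrolled, controls included, so as written it reports about half the true uptake and is capped at about 50%

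*Protocol article*

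**What the plan says.** Section 1.4 (Research questions) lists the adoption rate of EMBOLDEN as the first secondary implementation question and defines it in brackets as "the proportion of participants enrolled in the study who attend at least one group session and receive at least one system navigation support session". This fixes both parts of the proportion. The denominator is participants enrolled in the study, and the numerator is those who used both components at least once.

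Four other places show who is in that denominator and who can reach the numerator:

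- **Trial design (1.3):** "The allocation ratio is 1:1 for the intervention and control arms".
- **Recruitment and retention (2.1.8):** gift cards go to "All participants enrolled in the study, regardless of group allocation", and each neighborhood cohort is planned "with a maximum of 50 participants (25 intervention, 25 control) to be enrolled in each Hamilton" or Toronto neighborhood.
- **Allocation concealment and implementation (2.2.2):** "Once informed consent is obtained, the participant will be enrolled, baseline data will be collected, and the Research Coordinator will then obtain" the allocation from REDCap. Enrolment therefore comes before arm assignment.
- **EMBOLDEN (2.1.3.1) and Usual care (2.1.3.2):** "The EMBOLDEN intervention will consist of usual care (see below) plus the following two core components", namely the weekly group sessions and the one-to-one navigation. Usual care participants find and use services on their own, with no help from the research or intervention team.

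**The concern.** A measure of uptake should be taken among people who were offered the programme. Controls are not offered either component, so they add to the denominator and can never add to the numerator. The result then depends on the allocation ratio as well as on how participants responded to the programme: the same behaviour in the intervention arm would give a different adoption rate under 2:1 allocation.

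The stake is interpretive. The article says it wants its implementation findings to inform decision-makers and later scale-up. A programme that most invited people took up could look as if only a minority did. The figure would also not be comparable with uptake in a setting that has no control arm.

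**Working it through.** The article states no expected or target adoption rate, so there is no figure of the plan's own to reproduce. The check is of what the definition yields.

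**Inputs**

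- Sites: 8 in Hamilton and 2 in Toronto, 10 in total (section 2.1.8).
- Planned maximum per site: 50 enrolled, 25 in each arm (sections 2.1.8 and 2.2.1).
- Total sample size: 250 to 500 (section 2.1.7).
- Permuted blocks of 2, 4 and 6, with a separate sequence for each site (section 2.2.1).
- Uptake in the intervention arm: not given. Values of 60% to 100% are assumed below for illustration.

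**Step 1: the ceiling.** Let n_I be the number in the intervention arm, N the number enrolled and u the true uptake in the intervention arm.

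- Rate as written = u × n_I / N.
- The maximum is at u = 1, which gives n_I / N.
- Per site: 25/50 = 50%.
- Trial at N = 500: n_I = 10 × 25 = 250, so 250/500 = 50%.
- Trial at N = 250: 125/250 = 50%.

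**Step 2: the size of the understatement at N = 500.**

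| Assumed uptake in intervention arm | Rate as written (out of 500) | Rate among those offered it (out of 250) |
|---|---|---|
| 100% | 250/500 = 50% | 250/250 = 100% |
| 90% | 225/500 = 45% | 225/250 = 90% |
| 80% | 200/500 = 40% | 200/250 = 80% |
| 60% | 150/500 = 30% | 150/250 = 60% |

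The ratio of the two columns is n_I / N = 0.5 whatever the uptake.

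**Step 3: how exact the 50% cap is.** A site's sequence can stop partway through a block.

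- With 50 at a site, the last block stops after an even number of places, so the largest excess of intervention over control is 2. That gives 26/50 = 52%.
- With 25 at a site, the stop is at an odd place, so the excess can be 3 (the first three places of a block of 6). That gives 14/25 = 56%.
- Across 10 sites these departures largely cancel. In 3,000 simulated trials, with the three block sizes assumed equally likely, the central 95% of intervention shares was 49.4% to 50.6% with 50 per site and 48.8% to 51.2% with 25 per site.

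The trial-wide ceiling is therefore 50% to within about one percentage point. Anyone enrolled but never randomized would also count in the denominator as worded and would lower the ceiling.

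**The case against.** The best defence is context. The bracketed definition explains the adoption rate of the intervention. The next question asks what dose participants received, also without naming an arm, and that can only mean the intervention arm. The navigation description likewise speaks simply of participants. Loose wording is a likelier explanation than a decision to count controls, and the full approved protocol, which is not shown, may state the denominator properly. This is plausible. But the article does state a denominator, and it elsewhere uses the same expression for both arms. It also names intervention participants where it means only them, as in Table 1 and the social network analysis. The written rule therefore still needs correcting.

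It is also fair to say that little hangs on the number. No target, progression rule, test or sample size depends on it. Correct uptake could be recovered from the attendance and navigation logs listed in Table 1. That limits the harm, but the defined rate would still be misleading.

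Some stronger readings are tempting, and the documents do not support them:

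- **That the rate can never exceed 50%.** This is exact only with exactly equal arms. Unfinished blocks allow slightly more.
- **That a misleading 95% confidence interval is planned for it.** Section 2.3.3.4 attaches confidence intervals to the primary implementation outcomes, and this one is listed as secondary.
- **That the equal emphasis of the hybrid design makes it a leading result.** That emphasis concerns implementation and effectiveness as a whole. It does not promote this one proportion.
- **That Table 1 contradicts section 1.4 on what adoption means.** The table's row is headed "Adoption (Organization level", so its level is explicit. Section 1.4 defines a participant-level rate on the spot. These are two labelled levels, and any preference between terms is a matter of style.

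**Conclusion.** The point holds as a denominator error in one secondary, descriptive implementation outcome. Read as written, the adoption rate is about half the uptake among those offered the programme, and its ceiling is about 50%. At an assumed 80% uptake with 250 per arm, it would be 40% instead of 80%.

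This rests on three things: enrolment meaning both arms, as the article uses it elsewhere; allocation close to 1:1; and no control receiving group or navigation sessions. The halving does not depend on the assumed uptake or on the final sample size. The treatment comparison on moderate-to-vigorous physical activity does not use this rate and is unaffected.

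**What to change.** In section 1.4, secondary implementation question i, replace the denominator. The adoption rate should be the number randomized to the intervention arm who came to one or more group sessions and had one or more navigation sessions, divided by all participants randomized to the intervention arm, whether or not they started the programme.

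With that wording the possible range is 0% to 100% (250/250 at full uptake).

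The cost is one phrase. Group attendance and participation in one-to-one sessions are already recorded in REDCap (section 2.3.1.2), so no data collection changes. Table 1 and its terminology can stay as they are.
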